### Sample size calculation

Due to the extensive number of targeted endpoints (n=61), a classical sample size calculation cannot be performed. Therefore, to estimate the required sample size, we based our analysis on the four most investigated sphingolipid species, which are also the species entering the ceramide scores used at the Mayo Clinic (
*i.e.* ceramide 16:0, ceramide 18:0, ceramide 24:0 and ceramide 24:1).
^
16
^
^,^
^
17
^ Further, we hypothesised for simplicity that log2-transformed pre-intervention sphingolipid levels are similar in both the intervention and the control groups (due to the randomisation). Next, we assumed a standard deviation of log2-transformed sphingolipid levels of 0.407, an effect size (expressed as a geometric mean ratio) of 1.19 and a correlation coefficient between pre-and post-intervention values of 0.8. To obtain these values, we used the raw data of the four sphingolipids mentioned above issued from a previous exercise intervention study conducted by Bergman
*et al*.
^
37
^ Specifically, we calculated the geometric mean of the sphingolipid concentrations post- and pre-exercise for the four primary endpoints (i.e. ceramide 16:0, ceramide 18:0, ceramide 24:0 and ceramide 24:1). We then calculated the ratio of the geometric means post- to pre-exercise. Finally, we averaged the geometric mean ratios obtained for these four endpoints and obtained a value of 1.194. We then log2-transformed 1.194 and obtained 1.19. Therefore, 1.19 is the log2-transformed geometric mean ratios of the post- to pre-exercise sphingolipid concentrations. In other words, the geometric means of the sphingolipid concentrations differ by a factor of 1.19 post- to pre-exercise in healthy individuals in the study conducted by Bergman
*et al.*
^
37
^ Finally, we analysed covariance (ANCOVA) to calculate the sample size. We obtained a result of 16 participants per group for a power of 80% (
Figure 3). Lastly, it should be pointed out that the planned repeating measurements will enhance precision.
^
72
^ The R code used to calculate the sample size is freely available on Open Science Framework.
^
73
^

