### Endpoints

The primary endpoints will be changes from pre- to post-intervention levels of the four most studied sphingolipid species, which are also included in the ceramide-based scores (
*i.e.* ceramide 16:0, ceramide 18:0, ceramide 24:0 and ceramide 24:1).
^
14
^ The secondary endpoints will be changes from pre- to post-intervention levels of the resting sphingolipid species to be acquired (n=57).

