### Statistical analyses

The trajectory over time of each lipid species will be modelled using linear mixed models with a random effect for each subject. To identify variables, we should include in the models, we drew a causal directed acyclic graph (DAG) using DAGitty.
^
74
^ Sex, body fat mass, CRF, and habitual physical activity were identified as variables to be included in the linear mixed models to reduce the outcome variation and improve the precision of the average causal effect of the intervention on the sphingolipidome (
Figure 4).
^
72
^ As explained above, the design will control food intake as each participant will be provided with individualised, pre-packaged meals for days 7 to 10. It is also assumed that age difference will not play a significant role as all participants will be between 20 and 29 years old. Therefore, the models will include fixed effects for time points, sex, fat body mass, CRF, physical activity, and a three-way interaction term between the group, time point and an indicator variable for time points following the intervention. Planned contrasts between the groups at each time point following the intervention will allow assessing differences in lipid concentrations between the groups after the intervention. P-values and confidence intervals will be adjusted for multiple testing using the Benjamini-Hochberg method.
^
75
^ We will use residual diagnostic plots to assess whether the model assumptions are met. If model assumptions are violated, lipid concentrations will be log-transformed. If the proportion of missing data is below 5%, a complete case analysis will be done. Otherwise, we will consider multiple imputations. Drop-outs will be replaced by recruiting new subjects to achieve the targeted sample size of 32 participants.

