**Figure 4. f4:**
[figure not shown]
Directed acyclic graph representing the intervention effect on sphingolipid levels. The intervention (HIIT vs physical rest) is defined as the exposure and sphingolipids as the outcomes. Due to the randomisation, the exposure has no ancestor. Thus, no variable influences simultaneously the exposure and outcomes, which implies that there is no confounding variable. Sex, body fat mass, CRF, and physical activity were identified as variables to be included in the statistical models to reduce the outcome variation and improve the precision of the average causal effect of the intervention on the sphingolipidome. Abbreviations: HIIT = high-intensity interval training, CRF = cardiorespiratory fitness, black triangle pointing to the right on green background = exposure, black bold vertical bar = outcomes, blue background = variables to be included in the statistical models to reduce the outcome variation and improve the precision of the average causal effect of the intervention. The figure was realised with
http://www.dagitty.net.

The significance level is set at α = 0.05, and all tests will be two-sided. All analyses will be done according to the intention-to-treat principle. Statistical analyses will be conducted using R (version 4.0.2 or later). Study results will be reported in compliance with the CONSORT statement.
^
76
^

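### The stated 80% power is for one ceramide at one time point, tested unadjusted at 0.05; it does not apply to the planned Benjamini-Hochberg-adjusted analysis of four ceramides at five times, whose power is not given

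*Protocol article*

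**What the plan says.** The Endpoints section of the Protocol article names four primary variables and no primary time: "The primary endpoints will be changes from pre- to post-intervention levels of the four most studied sphingolipid species". The study procedure takes blood spots at five post-intervention times (2, 15, 30 and 60 min, and 24 h) and on three mornings beforehand.

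The Sample size calculation section uses a "standard deviation of log2-transformed sphingolipid levels of 0.407" and "an effect size (expressed as a geometric mean ratio) of 1.19 and a correlation coefficient between pre-and post-intervention values of 0.8". The effect is a single common value: "we averaged the geometric mean ratios obtained for these four endpoints and obtained a value of 1.194". The result is: "We obtained a result of 16 participants per group for a power of 80" per cent. The Figure 3 legend repeats it. The section adds, without a figure, that the repeated measurements will improve precision.

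The Statistical analyses section then sets out "Planned contrasts between the groups at each time point following the intervention", and says: "P-values and confidence intervals will be adjusted for multiple testing using the Benjamini-Hochberg method". The set of tests over which BH runs is not defined. The same section closes with: "The significance level is set at α = 0.05, and all tests will be two-sided".

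**The concern.** The protocol sizes one analysis and plans another. Neither the number of ceramides, nor the number of times, nor an adjusted significance level appears among the inputs to the 80%. The analysis has 4 x 5 = 20 group contrasts on the primary ceramides, and their p-values are adjusted.

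At stake is how the results are read. If 80% is taken to be the power of the primary analysis, an adjusted ceramide contrast that misses significance looks like a well-powered negative. Whether it is one depends on how many times respond and on how much the repeated baselines help, and the protocol quantifies neither.

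**Working it through.** **Inputs.** From the Sample size calculation section: geometric mean ratio 1.19, SD 0.407 (log2), correlation 0.8, 16 per group, ANCOVA. From the Statistical analyses section: two-sided 0.05. The sample size section states no alpha and its R code is not part of the document, so the unadjusted 0.05 is inferred from the match below.

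**Reproducing the stated figure.**
- Effect: log2(1.19) = 0.2510.
- ANCOVA residual SD: 0.407 x sqrt(1 - 0.8²) = 0.407 x 0.6 = 0.2442.
- Noncentrality at 16 per group: 0.2510 / (0.2442 x sqrt(2/16)) = 2.907.
- Noncentral t, df = 2 x 16 - 3 = 29, two-sided 0.05: power **0.802**. At 15 per group it is 0.774.

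Sixteen is thus the smallest group size that reaches 80% for one contrast, with nothing left over for adjustment.

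**Power after BH.** I simulated 32 participants with these inputs (6,000 runs per pattern). Each ceramide at each time was analysed by ANCOVA on baseline, and BH at 5% was applied over the 20 contrasts. Assumptions not in the document: the BH family is the 20 primary contrasts; correlation is 0.8 between any two times and 0.5 between ceramides; all four ceramides rise by 1.19 at each responding time.

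For three baselines, the covariate is their mean. Under equal correlation 0.8, its correlation with a later value is 0.8 / sqrt((1 + 2 x 0.8)/3) = 0.859. The residual SD becomes 0.407 x sqrt(1 - 0.859²) = 0.208, and the unadjusted formula power 0.909.

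| Times that respond | Per-contrast power, one baseline | Per-contrast power, mean of three baselines | Power for a given ceramide at one or more responding times, one baseline |
|---|---|---|---|
| 5 | 0.73 | 0.88 | 0.93 |
| 4 | 0.69 | 0.86 | 0.89 |
| 3 | 0.64 | 0.82 | 0.83 |
| 2 | 0.56 | 0.77 | 0.70 |
| 1 | 0.48 | 0.68 | 0.48 |

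Simulation error is about 0.01. In the same runs, unadjusted power is about 0.79 with one baseline and 0.90 with three. Both lie slightly below the formula values, because the formula ignores chance baseline imbalance.

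**Sensitivity to the correlation between ceramides.** With one baseline and all five times responding, per-contrast power is 0.74, 0.72 and 0.71 for correlations of 0, 0.5 and 0.8. With one time responding it stays at about 0.48. This assumption therefore matters little for per-contrast power.

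**The case against.** Four arguments favour the protocol, and most of them stand in part.

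- **BH is not Bonferroni.** This stands. A reader might divide 0.05 by 4 or 20 and conclude that power is 60% or 37%. Those are Bonferroni values, and the protocol specifies BH. Over 20 contrasts, BH power falls to about 0.36 only if a single contrast is real, whereas the hypothesis is a general rise in sphingolipids.
- **The repeated measurements are left out of the 80%.** This also stands. With three baselines, adjusted per-contrast power exceeds 80% when three or more times respond. A rise from 2 to 60 min that has gone by 24 h is still temporary, as hypothesised, and has about 0.86. A reader might infer that the primary analysis simply lacks the stated power. The document does not support that. What it shows is that the power is unstated and conditional.
- **Primary success is not defined.** On the laxer rule of a given ceramide being significant at one or more responding times, one baseline is enough for more than 80% if at least three times respond. This widens the range. It does not make the 80% the power of any adjusted test.
- **This is a pilot, and the BH family may be set in an analysis plan that is not shown.** The article does call the trial a pilot, describes its calculation as simplified, and nowhere says that it will read non-significance as a powered negative. The family of 20 is my assumption. Even so, the article prints 80% power twice without saying that it excludes the adjustment it plans.

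**Conclusion.** The point holds as a mismatch between the stated power and the planned analysis. The 80% is correct arithmetic for one ceramide, one time, one baseline and unadjusted two-sided 0.05. It does not apply to the adjusted comparison of four ceramides at five times.

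On the protocol's inputs with one baseline, adjusted per-contrast power is below 80% in every pattern tried, at about 0.48 to 0.73. With the three planned baselines credited it is about 0.68 to 0.88, and below 80% only if one or two times respond. The shortfall is thus real for a brief rise and absent for a broad one, once the baselines are counted.

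These figures rest on a common ratio of 1.19 for every responding contrast, equal correlation 0.8 over time, and BH over 20 contrasts. The model covariates (sex, fat mass, fitness, activity) could add precision, but the document gives no figure for that and none is credited here. No planned test is invalid.

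**What to change.** In the Sample size calculation section and the Figure 3 legend, state that 80% is the power of a single contrast at unadjusted two-sided 0.05 with one baseline. Next to it, report the BH-adjusted power as a range with its assumptions: about 0.48 to 0.73 with one baseline and 0.68 to 0.88 with three, according to the number of responding times. Say over which set of tests BH was taken to run. Do not quote 60% or 37% as the adjusted power. In the results, do not present a non-significant adjusted contrast as a negative finding with 80% power.

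The cost is wording and a less favourable power statement; no data or participants are added.

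Naming one averaged contrast per ceramide as primary is optional and has a price. It is less sensitive if the rise is confined to one time. With the study status given as data analysis, it would also be a late endpoint change, to be fixed before group results are seen and reported as such.

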**Figure 3. f3:**
[figure not shown]
Illustrated sample size calculation. A sample size of 16 participants per group was obtained (expressed as a detectable geometric mean ratio), assuming a power of 80%, an effect size of 1.19 (expressed as a geometric mean ratio), a standard deviation of 0.407 and a correlation coefficient ρ between pre-and post-intervention values of 0.8.

### Statistical analyses

The trajectory over time of each lipid species will be modelled using linear mixed models with a random effect for each subject. To identify variables, we should include in the models, we drew a causal directed acyclic graph (DAG) using DAGitty.
^
74
^ Sex, body fat mass, CRF, and habitual physical activity were identified as variables to be included in the linear mixed models to reduce the outcome variation and improve the precision of the average causal effect of the intervention on the sphingolipidome (
Figure 4).
^
72
^ As explained above, the design will control food intake as each participant will be provided with individualised, pre-packaged meals for days 7 to 10. It is also assumed that age difference will not play a significant role as all participants will be between 20 and 29 years old. Therefore, the models will include fixed effects for time points, sex, fat body mass, CRF, physical activity, and a three-way interaction term between the group, time point and an indicator variable for time points following the intervention. Planned contrasts between the groups at each time point following the intervention will allow assessing differences in lipid concentrations between the groups after the intervention. P-values and confidence intervals will be adjusted for multiple testing using the Benjamini-Hochberg method.
^
75
^ We will use residual diagnostic plots to assess whether the model assumptions are met. If model assumptions are violated, lipid concentrations will be log-transformed. If the proportion of missing data is below 5%, a complete case analysis will be done. Otherwise, we will consider multiple imputations. Drop-outs will be replaced by recruiting new subjects to achieve the targeted sample size of 32 participants.

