### Group allocation

Participants will be randomly allocated either to the HIIT (n= 16, 50% females) or control (n= 16, 50% females) groups. Blocked randomisation will be used to reduce bias and achieve balance in allocating participants to both groups, as commonly done when the sample size is small.
^
60
^ The principal investigator will be responsible for the randomisation and will inform participants and investigators about the group allocation only on the day of the intervention (
*i.e.* opening of the sealed envelope). Therefore, participants and investigators supervising the intervention will be blinded for group allocation till the day of the intervention. The laboratory team in charge of the sphingolipid quantification will be blinded for group allocation.

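### The trial is sized on a log2 ratio, but the analysis defaults to untransformed concentrations and moves to logs only if residual plots look poor, so the effect measure is not fixed in advance

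*Protocol article*

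**What the plan says.** **Sample size calculation (Protocol article).** The planning scale is explicit: "Next, we assumed a standard deviation of log2-transformed sphingolipid levels of 0.407, an effect size (expressed as a geometric mean ratio) of 1.19", with a pre-post correlation of 0.8. The method is ANCOVA, and the result is "We obtained a result of 16 participants per group for a power of 80" per cent. The effect is the average of four ceramide post-to-pre geometric mean ratios, so it is multiplicative by construction. The Figure 3 legend repeats the same inputs.

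**Statistical analyses (Protocol article).** A linear mixed model with a random effect per subject is fitted to each lipid species. Planned contrasts compare lipid concentrations between the groups at each time point after the intervention. Residual plots are then inspected, and: "If model assumptions are violated, lipid concentrations will be log-transformed". No criterion for a violation and no log base are given, and the section does not say whether a switch would apply to one species or to the whole panel.

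**Endpoints and Table 1.** The primary endpoints are changes in levels of ceramides 16:0, 18:0, 24:0 and 24:1. Table 1 calls the outcome a concentration. Neither names a scale.

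**The concern.** The two sections describe different effects. A model on untransformed values estimates a difference in arithmetic means, in concentration units. A model on log2 values estimates a difference that back-transforms to a ratio of geometric means. The trial was sized for the second, and the analysis rule begins with the first.

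The move from one to the other changes the quantity being estimated as well as the fit. Here it is triggered by judging residual plots of the outcome data. Until those data have been modelled, a reader cannot say whether the primary result for a given ceramide will be a difference or a ratio, or whether it can be set beside the planned 1.19.

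If the check is made separately for each model, some species could be reported as differences and others as ratios. That would make the panel hard to read as a whole. It would also weaken the aim stated in the Discussion, that the trial's effect estimates should feed power calculations for later studies.

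**Working it through.** **Inputs, all from the protocol article**
- Log2 SD 0.407, geometric mean ratio 1.19, correlation 0.8, ANCOVA, 80% power, 16 per group (Sample size calculation).
- Two-sided α = 0.05 (text below the Figure 4 legend).
- Equal arms of 16 (Group allocation).

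**Step 1. Reproduce the stated sample size.**
- Effect on the log2 scale: log2(1.19) = 0.251.
- ANCOVA residual SD: 0.407 × √(1 − 0.8²) = 0.407 × 0.6 = 0.2442.
- Normal approximation: n = 2 × [(1.960 + 0.842) × 0.2442 / 0.251]² = 14.9, so 15 per group.
- Noncentral t with 16 per group: noncentrality 0.251 / (0.2442 × √(2/16)) = 2.91. Power is 0.802 (29 df) to 0.803 (30 df). With 15 per group it is about 0.775.
- Hence 16 per group, as stated.
- Other readings at a ratio of 1.19, by the normal approximation: log2 change score 17, log2 post-only 42, SD taken as natural-log 31.

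The planned effect is therefore a ratio analysed on log2 values.

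**Step 2. What the planning figures imply on the raw scale, if levels are lognormal.**
- Natural-log SD: 0.407 × ln 2 = 0.282.
- Marginal CV: √(exp(0.282²) − 1) = 0.288. Marginal skewness: (exp(0.282²) + 2) × 0.288 = 0.89.
- These describe the spread between people. The residuals of a random-intercept model are less skewed. If 0.8 is read as an intraclass correlation (an assumption), the within-subject log2 SD is 0.407 × √0.2 = 0.182. The within-subject CV is then about 13% and the residual skewness about 0.4.
- A 1.19-fold multiplicative effect would multiply the HIIT arm's raw variance by 1.19² = 1.42. With no effect the factor is 1.

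The departure from the raw-scale model is moderate, so different readers of the plots could reasonably disagree.

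**Step 3. What the rule does to power and type I error.** Simulation with lognormal data, the inputs above, 16 per arm, one pre and one post value, ANCOVA and 10,000 runs. A Shapiro-Wilk p < 0.05 on the raw-model residuals stands in for the visual check. That stand-in is an assumption, since the protocol gives no criterion.

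| Analysis | Power at ratio 1.19 | Type I error |
|---|---|---|
| Log2 always | 0.790 | 0.048 |
| Raw always | 0.765 | 0.047 |
| Raw, switch to log if residuals fail | 0.774 | 0.049 |
| Better of the two p-values | 0.807 | 0.056 |

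The last row is a worst case that the protocol does not propose. The rule switched to log in 16% of runs (0.157 with no effect, 0.165 at ratio 1.19). Even with truly lognormal data, it usually stayed on the raw scale.

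**Step 4. How often the four primary ceramides would end on mixed scales (illustration only).** If the switch were made per species, independently and at a rate of 0.16: 1 − 0.84⁴ − 0.16⁴ = 1 − 0.498 − 0.001 = 0.50. Correlated species or another diagnostic would change this figure. If one decision covered all species, it would be zero.

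**The case against.** The strongest case on the other side has four parts.

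- **The rule is stated in advance.** It gives a default, a trigger and one fallback, which is not an open choice. Residual plots need not display the group contrast, and the laboratory is blinded to allocation. This is fair and limits the room for bias. It does not settle which effect measure will be reported.
- **Raw concentrations agree with the endpoint definition.** Endpoints and Table 1 speak of levels and concentrations, so a raw-scale model does not contradict them. That stands. The mismatch is between the analysis and the sample size basis.
- **Detail may sit in a fuller document.** A criterion, a log base and a reporting format are things an article may leave to an analysis plan, and their absence alone would be no finding. But the article states a specific default that departs from its own planning scale. A later document would have to overturn that rule, since added detail alone would not remove the mismatch.
- **The numerical harm is small.** Step 3 supports this. Equal arms also limit what unequal variance does to between-group tests, and the stated response to it is the log transformation.

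A reader might infer that the scale will certainly be chosen species by species. The protocol does not say so. It follows naturally from fitting one model per species, but a single switch for all species fits the wording equally well.

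**Conclusion.** The point holds as a should-fix. The sizing is on log2 levels and a ratio, the analysis defaults to untransformed concentrations, and nothing in the article reconciles them. The primary effect measure is left to outcome residuals and may not match the planned effect. It could also differ between species, if the switch is made model by model.

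The size of the problem lies in the estimand and hardly at all in error rates. Power is about 0.79 on the log scale against 0.77 on the raw scale or under the switch, and type I error is about 0.05 throughout. These figures assume lognormal data, the protocol's SD and correlation, a simplified one-pre, one-post ANCOVA, and a formal test in place of visual judgement.

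Three stronger readings are tempting, and the documents do not support them:
- **That the sample size is wrong.** It reproduces, and it stays at 16 per group with the scale fixed.
- **That the switch materially inflates false positives.** It gives 0.049. Even picking the better of two scales gives only 0.056.
- **That raw-scale residuals would be badly skewed.** The 0.89 is a marginal figure. The residual value is about 0.4 under the intraclass reading of 0.8.

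**What to change.** Replace the conditional rule in Statistical analyses with a fixed one:

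- Log2 concentration is the primary analysis scale for the four primary ceramides and, for consistency, for the other 57 species.
- Each contrast is back-transformed and reported as a geometric mean ratio with its confidence interval.
- Residual diagnostics are still examined, but they can only trigger a sensitivity analysis (raw scale, robust or bootstrap). They do not change the primary scale.

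**Cost.** The text change is short. No new sample size is needed, because 16 per group was already derived on this scale, and under lognormal data power rises slightly. The cost is procedural: Table 1 and Study status both give data analysis as the current stage. The change must therefore be dated and documented as made before unblinded group contrasts were read. If that cannot be shown, it should be disclosed as post hoc.
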